## Analysis

3

The primary analysis principle applied will be intention-to-treat. The only condition for initial inclusion is application of the correct wound dressing at the end of the procedure. Exclusion criteria are early death or re-operation before being able to assess proper wound healing and thus primary or secondary endpoints. Early deaths or reoperations due to SSI are registered as SSIs.

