### Enrollment and randomization

2.5

Patients scheduled for lower limb revascularization are provided with written information prior to undergoing the admission procedure which takes place one to two weeks prior to scheduled surgery. During the admission process, the background and aim of the study are discussed with eligible patients, informed consent obtained and the randomization conducted by outpatient clinic nurses. In this study we apply simple randomization using an opaque randomization envelope containing equal numbers of “PICO” and “standard” notes. In bilateral groin incisions, the draw from the envelope dictates the wound dressing selection in the right inguinal incision and the contralateral incision is automatically assigned the alternate dressing. Randomization outcome and consent form are documented in the patient's records.

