A potential limitation of this study could be that the randomization takes place before the operation, not at its end. One might argue that this could create bias since the surgeon in charge, could be aware of the respective randomization outcome before conducting the operation and thereby subconsciously or consciously modify their behavior and surgical technique. Because of the large staff turn-over in the operation room, an intraoperative randomization would most likely have led to a very large number of patient dropouts due to insufficient sense of awareness for the study and the principal investigator felt that intraoperative computer-generated randomization not seems feasible. Use of randomization envelopes in the operation room was not felt as an option either due to issues of management of these envelopes and the large turnover of personnel at present times. When wound closure has been performed, the surgeon usually leaves the operation room and the scrub nurse finalizes the wound care including application of wound dressings. That is usually the time to take a look at the randomization results in the patient files, which should minimize bias due to behavior issues. At present time, four vascular centers will be enrolling patients into the study and these centers does not, for instance, have identical perioperative wound care. The type of standard wound dressing used in the control arm might differ. We will, however, document the type of wound dressing and perform sub analysis accordingly. Generalizability of the results will be better in a multi-centre trial including both university hospitals and county hospitals.

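### The primary analysis is labelled intention-to-treat, but the analysis set is restricted after randomisation to groins that received the correct dressing

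*Protocol article*

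**What the plan says.** Section 3 (Analysis) opens with "The primary analysis principle applied will be intention-to-treat". The next sentence reads "The only condition for initial inclusion is application of the correct wound dressing at the end of the procedure". A third removes further groins: "Exclusion criteria are early death or re-operation before being able to assess proper wound healing and thus primary or secondary endpoints". Early deaths and re-operations caused by SSI are kept and counted as SSI.

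Section 2.5 (Enrollment and randomization) sets the timing. Patients are told of the study, consent and are randomised during "the admission procedure which takes place one to two weeks prior to scheduled surgery", with "informed consent obtained and the randomization conducted by outpatient clinic nurses". The Discussion confirms that "the randomization takes place before the operation, not at its end" and concedes that "the surgeon in charge, could be aware of the respective randomization outcome before conducting the operation".

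Sections 2.8.1 and 2.8.2 list the randomised dressing and the dressing received as separate data items. Nowhere does the article say that a groin given the wrong dressing stays in the arm it was drawn for.

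**The concern.** Intention-to-treat means analysis by allocation, whatever was received. A requirement that the correct dressing was applied selects on treatment received, at a moment one to two weeks after the draw. The two sentences cannot both define the primary set.

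The stake is the protection that randomisation gives. If groins that get the wrong dressing differ in infection risk from the rest, removing them shifts the SSI rate of the arm that loses them, even when the dressing has no effect. The report would then present a result from a selected set as intention-to-treat, on the primary endpoint. The article says that its methods are published ahead of analysis in order to avoid bias, so this definition should be settled now.

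**Working it through.** **1. Can the condition be read as an enrolment criterion?**

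- Randomisation: admission visit, one to two weeks before surgery (section 2.5), and before the operation (Discussion).
- Condition: dressing applied at the end of the procedure (section 3).
- Eligibility (section 2.4): adults having elective procedures with lower-limb arterial exposure, with no mention of the dressing.

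The condition can be met only after allocation and it stands in the Analysis section. It can act only as a post-randomisation filter.

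**2. The plan's own sample size, for reference.** Inputs from section 3.2: TEA, SSI 20% against 8%, 80% power, 5% significance, Fisher's exact test, n1 = 284. Full enumeration of the two-sided exact test gives 80.2% power at 142 per arm and 79.5% at 140 per arm, so n1 = 284 reproduces. For bypass (40% against 15%), power is 80.8% at 56 per arm, so n1 = 112 reproduces too. The contradiction does not depend on these figures; they are the baseline for step 4.

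**3. Possible shift from excluding wrongly dressed groins.** The documents give no wrong-dressing rate and no risk for such groins. Assume no true effect, SSI rate r = 20% in both arms, and a share c of one arm dropped at twice the average risk (40%). The rate left in that arm is

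(r − c × 2r) / (1 − c)

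- c = 5%: (0.20 − 0.05 × 0.40) / 0.95 = 0.18 / 0.95 = 18.9%, a shift of 1.1 points.
- c = 10%: (0.20 − 0.10 × 0.40) / 0.90 = 0.16 / 0.90 = 17.8%, a shift of 2.2 points, or 2.2 / 12 = 18% of the targeted difference.

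If the NPWT arm loses these groins, NPWT looks better than it is. If the control arm loses them, NPWT looks worse by the same amount. At the bypass rate of 40%, dropping 5% at twice the risk gives (0.40 − 0.05 × 0.80) / 0.95 = 37.9%, a shift of 2.1 points.

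**4. The price of analysing as randomised.** Suppose a share c of each arm receives the other dressing and is kept in its allocated arm. The arm rates become

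- control: 0.20(1 − c) + 0.08c
- NPWT: 0.08(1 − c) + 0.20c

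and the difference is 0.12(1 − 2c).

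| Crossover in both arms | TEA difference | Power, unilateral TEA (n = 284) | Power, unilateral bypass (n = 112) |
|---|---|---|---|
| 0% | 12.0 points | 80.2% | 80.8% |
| 2% | 11.5 points | 76.5% | 77.1% |
| 5% | 10.8 points | 70.4% | 71.0% |
| 10% | 9.6 points | 59.1% | 59.5% |

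If 10% of the NPWT arm alone crosses over, its rate is 0.9 × 0.08 + 0.1 × 0.20 = 9.2%, and power for unilateral TEA is 68.7%.

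**The case against.** The contradiction between the two sentences is hard to dispute, but several stronger readings that a reader might draw do not hold.

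- **That the set is per-protocol in the full sense.** The condition concerns only the dressing put on at the end of surgery. Section 2.7 describes seven days of wear, and nothing in section 3 removes groins whose dressing came off early or whose pump failed. The set is defined by starting the allocated treatment, so allocated-and-started describes it at least as well. It is still not intention-to-treat.
- **That staff will move high-risk wounds from one dressing to the other.** The documents describe no such practice. The Discussion's concession is about the surgeon's behaviour and technique. It adds that the surgeon has usually left when the scrub nurse applies the dressing, and that the allocation is usually looked up then. Plain look-up errors could be unrelated to risk and would cause little bias.
- **That the bias favours NPWT.** The direction depends on which arm loses groins and which groins they are. The documents settle neither.
- **That the bias is large.** With no true effect and 142 groins kept in each arm for simplicity, the two-sided Fisher test rejects in 3.6% of trials without selection, 4.0% in the 5% scenario and 5.6% in the 10% scenario. Removing the dropped groins from the count raises the last two figures a little. This supports a correction but not a claim of major distortion.
- **That the sample size makes no allowance for wrong dressings.** The 10% addition gives missing data and re-operations as examples only, so the list is open.
- **That keeping crossovers costs almost nothing.** The table above shows otherwise.

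These points limit what may be claimed about size and direction. None of them reconciles the label with the rule.

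**Conclusion.** The plan is wrong as written. Its primary set is selected after randomisation on treatment received, and the result would be mislabelled intention-to-treat. This conclusion rests on the text alone and needs no numerical assumption.

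The size and direction of any bias are unknown. The shift of 1.1 to 2.2 points assumes no true effect, 20% SSI, 5% to 10% of one arm dropped, and twice the average risk in those groins. The last two are illustrative values without a source in the documents. If every groin receives its allocated dressing, the condition removes nobody, but that cannot be assumed in advance: the article itself cites high staff turnover and limited awareness of the study in the operating room.

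The exclusion of early deaths and re-operations not due to SSI is a second departure from the label. It would remain if only the dressing condition were deleted.

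**What to change.** 1. Delete the correct-dressing condition from section 3.
2. Define the primary set along these lines: all randomised groins that undergo an inguinal incision are analysed in the arm allocated, whatever dressing was applied.
3. Report the correct-dressing set as a labelled per-protocol sensitivity analysis.
4. Reconcile the following sentence with the label: state how randomised groins with early death or re-operation not due to SSI enter the primary analysis, or stop calling the analysis intention-to-treat.
5. Report the number of wrong dressings by arm.

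This needs a few sentences and no new data, since the allocated and the received dressing are both already recorded. The real cost is the loss of power from crossovers shown in the working. It is a reason to keep wrong dressings few and to count them openly, and does not justify excluding them from the primary set. If the sponsor prefers to keep the restricted set as primary, it should be named for what it is.

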## Introduction

1

Lower limb revascularization relies on access to the common femoral artery. The inguinal region contains, however, a high concentration of virulent bacteria [1] due to its close proximity to the perianal region and open lower limb revascularization is associated with increased risk of surgical site infections (SSI). Meticulous surgical technique during open vascular surgery is necessary to minimize the risk of postoperative lymphatic wound complications [2]. Both patient- and procedure-related factors contributes to the risk for surgical site infections (SSI) [3]. It appears that extension of incisions are associated with increased risk of SSI during open vascular procedure [4]. Prospective series on open lower limb revascularization is not seldom associated with SSI rates of more than 20% [5]. Apart from being common, consequences may be devastating as severe deep SSI may lead to severe bleeding complications and/or limb loss and/or death.

Negative pressure wound therapy (NPWT) on closed, clean incisions, has emerged as a prophylactic option to reduce the risk of SSI in high-risk incisions [[6], [7], [8]]. A recent meta-analysis on randomized control trials (RCT) compared NPWT to standard dressing for closed groin incisions after vascular surgery and found a reduced SSI rate. This meta-analysis relied on the use of Prevena™ NPWT system. No RCT has been published using the alternative PICO™ device on vascular surgical incisions. In contrast to Prevena™, PICO™ is a canisterless, disposable NPWT system, where the dressing pad works mainly by evaporation of fluid [9]. NPWT decreases hematoma and seroma formation mainly by enhancing the endogenous draining capacity of the lymphatic system [10]. NPWT induces less biomechanical stress around skin and subcutaneous suture lines [11], which probably facilitate tissue apposition creating a better microbial barrier and decrease scar formation. There appear to be little perfusion changes around the wound edges measured by laser Doppler velocimetry before and after application of PICO™ on incisional wounds [12].

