### Study objectives

2.1

The study was initiated to determine whether a prophylactic negative pressure wound therapy pad (PICO™) applied after vascular surgical procedures with inguinal incisions could reduce the surgical site infection rate as well as the frequency of other wound complications such, seroma/lymphocele, hematoma and wound dehiscence when compared to the standard wound dressing.

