### Endpoints

2.2

The primary endpoint is the SSI rate and secondary endpoints are the rate of seroma/lymphocele, hematoma and wound dehiscence within the first 90 days postoperatively.

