#### Follow-up data

2.8.3

Readmission within 30 days postoperatively (yes/no), surgical site infection (SSI) within 30 days (yes/no), wound culture obtained within first 3 months postoperatively (yes/no), reoperation 30 days (yes/no), sought medical attention because of groin problem within 90 days (yes/no), reoperation 90 days (yes/no), SSI 90 days (yes/no), reoperation 1 year (yes/no), SSI 1 year (yes/no), wound cultures within 1 year (yes/no), 1 year mortality (yes/no), mortality due to groin infection (yes/no), type of bacterial isolate, SSI severity grading according to Szilagyi classification [16], C-reactive protein concentration at infection diagnosis (mg/L), presenting symptoms, surgical revision (yes/no), negative pressure wound therapy after surgical revision (yes/no), sepsis (yes/no), bleeding (yes/no), wound dehiscence (yes/no), seroma (yes/no), hematoma (yes/no), lymphorrhea (yes/no), amputation within 1 year (yes/no). Adverse events of the NPWT dressing (yes/no) and type of adverse events.

The diagnosis SSI is made according to the 1999 diagnostic criteria defined by the Centers for Disease Control and Prevention, USA [17]. Wound outcome will be objectively evaluated with the validated ASEPSIS score [18]. The wound score is based upon the following criteria: Antibiotics (10 points), drainage of pus under local anaesthesia (5 points), debridement of wound (general anaesthesia) (10 points), serous discharge, erythema, purulent exudate, separation of deep tissue within the first week (5 points each), isolation of bacteria (10 points), stay as inpatient prolonged over 14 days (5 points). A total score ≥21 points is considered as infection, 11–20 points as disturbance of healing, 0–10 points as satisfactory healing. SSI along surgical incisions for exposure of arteries will be assessed. The data analysis and subsequent establishment of the diagnosis SSI or other wound complications is done under blinded conditions. The assessor at the outpatient clinic at one month and at one year does not know whether a particular groin incision was treated with NPWT or the standard wound dressing.

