**Table 1 tbl1:**
[figure not shown]
Characteristics of the two main types of procedures studied.

Taking into account the previously identified 1-year mortality of 13.9%, yields a mortality-corrected sample size of n = 325 (280/(1–0.139)).

In an attempt to adjust for other types of “loss to follow-up” such as missing data and re-operations on the respective side, we added an additional 10% (33 cases) resulting in a total sample size of 358. **BYPASS** Previous data indicated an SSI rate after bypass of 41.1% when using the standard dressing. Assuming all cases are either unilateral or bilateral, and a reduction in SSI rate from 40% to 15% with a proportion of discordant pairs of 40% in bilateral cases yields n1 = 112 and n2 = 93, respectively. Among all bypass cases, 90% are assumed to be unilateral (i.e. p1 = 0.90) **(**Table 1**)**:n = p1 *n1 + (1 - p1) *n2. n = 0.90 * 112 + 0.10 * 93 = 110

The 1-year mortality in this group was 8.9%, yields a mortality-corrected sample size of n = 121 (110/(1–0.089)). To adjust for other types of “loss to follow-up”,we added an additional 10% (12 cases) resulting in a total sample size of 133.

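### Early re-operation for haematoma, seroma/lymphocele or dehiscence appears to remove a groin from the analysis instead of counting as that secondary endpoint, contrary to the declared intention-to-treat principle

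*Protocol article*

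**What the plan says.** The Analysis section (3) opens with "The primary analysis principle applied will be intention-to-treat". It then sets an exclusion at the analysis stage: "Exclusion criteria are early death or re-operation before being able to assess proper wound healing and thus primary or secondary endpoints". One exception follows: "Early deaths or reoperations due to SSI are registered as SSIs".

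The complications that could also prompt an early return to theatre are endpoints of the trial. Section 2.2 says "secondary endpoints are the rate of seroma/lymphocele, hematoma and wound dehiscence within the first 90 days postoperatively", and the Study objectives (2.1) name the same outcomes: "as well as the frequency of other wound complications such, seroma/lymphocele, hematoma and wound dehiscence". The Introduction gives the expected direction: "NPWT decreases hematoma and seroma formation mainly by enhancing the endogenous draining capacity of the lymphatic system".

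The sample size section (3.2, text after Table 1) places re-operations with missing data under loss to follow-up: "re-operations on the respective side, we added an additional 10% (33 cases) resulting in a total sample size of 358". The bypass group gets a corresponding 10% (12 cases, total 133).

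Follow-up data (2.8.3) include "reoperation 90 days (yes/no), SSI 90 days (yes/no), reoperation 1 year (yes/no", together with yes/no items for haematoma, seroma, dehiscence and surgical revision.

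**The concern.** A groin taken back early because of a haematoma or dehiscence has had a severe form of a secondary endpoint. The exclusion rule has a counting provision for SSI and none for these outcomes, so such a groin appears to be dropped and its event lost.

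Three consequences follow:

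- **Conflict with intention-to-treat.** The exclusion happens after randomisation and depends on what happened to the wound.
- **Secondary endpoints.** If the dressing works as the Introduction expects, more control groins than NPWT groins are re-operated for these reasons and removed. The absolute difference then moves toward zero.
- **Primary endpoint.** The same rule defines who enters the SSI comparison, so that comparison is made on groins selected by an outcome the dressing is meant to change. In bilateral cases, losing one groin also breaks the pair that McNemar's test (section 4) needs.

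**Working it through.** **1. The plan's own figures.**

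- TEA: 0.95 × 284 + 0.05 × 210 = 280.3, taken as 280. Then 280/(1 − 0.139) = 325.2, taken as 325. Then 10% of 325 = 32.5, taken as 33. Total 358.
- Bypass: 0.90 × 112 + 0.10 × 93 = 110.1, taken as 110. Then 110/(1 − 0.089) = 120.7, taken as 121. Then 10% of 121 = 12.1, taken as 12. Total 133.

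Both totals reproduce, and this point does not change them. TEA before losses is 358/2 = 179 groins per arm. That is the base on which an exclusion acts.

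**2. Who leaves the analysis, taking the passages together.**

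| Early event | Rule in section 3 |
|---|---|
| Re-operation or death due to SSI | Registered as SSI |
| Re-operation for haematoma, seroma/lymphocele or dehiscence | No counting rule; falls under the exclusion on its most natural reading |
| Re-operation for another reason, before healing can be assessed | Excluded |

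The article does not define early.

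**3. Illustration of size (all rates assumed).** The article gives no haematoma, seroma, dehiscence or re-operation rates. Let p be the true event rate in an arm and f the share of events re-operated early and excluded, with f equal in both arms.

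- Events removed per arm = 179 × p × f
- Rate observed after exclusion = p(1 − f)/(1 − pf)

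For 10% (control) versus 5% (NPWT), a true difference of 5.0 points:

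| f | Removed, control vs NPWT | Observed rates | Observed difference |
|---|---|---|---|
| 25% | 4.5 vs 2.2 | 0.075/0.975 = 7.7% vs 0.0375/0.9875 = 3.8% | 3.9 points |
| 50% | 9.0 vs 4.5 | 0.050/0.950 = 5.3% vs 0.025/0.975 = 2.6% | 2.7 points |
| 75% | 13.4 vs 6.7 | 0.025/0.925 = 2.7% vs 0.0125/0.9625 = 1.3% | 1.4 points |

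For 20% versus 10%, a true difference of 10.0 points, the observed difference is 8.1, 5.8 and 3.2 points at the same three values of f.

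**4. Scale of the effect measure.** With equal f, the risk ratio hardly moves. At 10% versus 5% the true ratio is 0.50, and after exclusion it is 0.0380/0.0769 = 0.49 at f = 25% and 0.0130/0.0270 = 0.48 at f = 75%. What shrinks is the absolute difference and the number of events that carry the comparison.

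The ratio is also pulled toward 1 if NPWT mainly prevents the severe events. Assume 6% versus 2% re-operated early and 6% milder events in each arm. The true rates are then 12% versus 8% (difference 4.0 points, ratio 0.67). After exclusion they are 0.06/0.94 = 6.4% versus 0.06/0.98 = 6.1% (difference 0.3 points, ratio 0.96).

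**The case against.** The strongest reply is that the exclusion is conditional. It applies only when re-operation comes before the endpoints can be assessed, and a groin re-operated for haematoma has arguably already shown a secondary endpoint. On that reading only groins in which nothing could be observed are dropped. Section 2.8.3 lends some support, since it records these complications, surgical revision and later re-operations, so data collection continues past a revision.

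This reading is possible, so a reader should not infer that the plan certainly deletes these events. But the article does not state it, and two features tell against it. If an observed event were enough to keep a groin, the explicit provision for SSI would be unnecessary, yet it is given for SSI alone. The sample size section also counts re-operations as loss.

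Three further objections stand in part:

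- **The 10% allowance is no measure of size.** A reader might take the 33 and 12 cases as the number of excluded re-operations. The allowance pools missing data and re-operations of every cause without a split.
- **The effect on SSI is not shown.** A reader might infer that re-operated groins carry more later SSI and that the primary result is biased in a known direction. The article gives nothing to support this, and re-operations due to SSI are retained as events.
- **A condensed article may leave detail to a fuller document.** That covers the definition of early, but not an exclusion rule the article itself states and that conflicts with its declared principle.

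**Conclusion.** The concern holds as a should-fix. As worded, the plan combines intention-to-treat with a post-randomisation, outcome-dependent exclusion. Its most natural reading removes groins re-operated early for haematoma, seroma/lymphocele or dehiscence, although these are secondary endpoints.

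If NPWT reduces these events, more control than NPWT events are lost and the absolute difference is biased toward zero. Under the assumed 10% versus 5% rates, with 25% to 75% of events excluded equally in both arms, the 5.0-point difference falls to between 3.9 and 1.4 points, a loss of 22% to 72%. The true size is unknown because the article gives no rates.

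The imbalance between arms depends on NPWT having the expected effect. The SSI analysis set also becomes outcome-dependent, but the direction of any SSI bias cannot be determined from the article. The demonstrated harm lies in the secondary endpoints and works against finding a benefit, so a stronger grade is not warranted.

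**What to change.** Replace the exclusion with these rules:

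1. Keep all randomised, operated incisions in the analysis.
2. Register an early re-operation for haematoma, seroma/lymphocele or dehiscence as that secondary event, parallel to the existing SSI rule.
3. Retain the groin for SSI ascertainment to day 90.
4. Report a sensitivity analysis that applies the exclusion as the article now words it.

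How deaths without SSI are counted is a separate choice and is not part of this change.

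The sample size is unaffected. The complications and re-operations are already recorded, but the listed follow-up items give re-operation as yes/no without a reason, so the reason must be taken from the patient records. The SSI rule already requires that judgement. One statistical cost remains: an SSI arising after a re-operation partly reflects the second procedure, which the sensitivity analysis helps to show. The Discussion says the article was published before enrolment was complete and before analysis, so the rule could still be settled ahead of the results.
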